## Abstract

**Introduction:**

Although breast reconstruction is an integral part of breast cancer treatment, there is little high-quality evidence to indicate which method is the most effective. Randomised controlled trials (RCTs) are generally thought to provide the most solid scientific evidence, but there are significant barriers to conducting RCTs in breast reconstruction, making both recruitment and achieving unbiased and generalisable results a challenge. The objective of this study is to compare implant-based and autologous breast reconstruction in non-irradiated patients. Moreover, the study aims to improve the evidence for trial decision-making in breast reconstruction.

**Methods and analysis:**

The study design partially randomised patient preference trial might be a way to overcome the aforementioned challenges. In the present study, patients who consent to randomisation will be randomised to implant-based and autologous breast reconstruction, whereas patients with strong preferences will be able to choose the method. The study is designed as a superiority trial based on the patient-reported questionnaire BREAST-Q and 124 participants will be randomised. In the preference cohort, patients will be included until 62 participants have selected the least popular alternative. Follow-up will be 60 months. Embedded qualitative studies and within-trial economic evaluation will be performed. The primary outcome is patient-reported breast-specific quality of life/satisfaction, and the secondary outcomes are complications, factors affecting satisfaction and cost-effectiveness.

**Ethics and dissemination:**

The study has been approved by the Swedish Ethical Review Authority (2023-04754-01). Results will be published in peer-reviewed scientific journals and presented at peer-reviewed scientific meetings.

**Trial registration number:**

NCT06195865.

STRENGTHS AND LIMITATIONS OF THIS STUDYThis protocol uses a partially randomised patient preference trial design to compare different techniques in breast reconstruction.The protocol includes studies within a trial to explore the research methodology further.The protocol’s outcomes measures include outcomes important to patients, professionals and society, such as patient-reported outcomes, complications and cost-effectiveness.The protocol’s conceptual risks include difficulty recruiting participants, especially to the randomised arm, and a low adherence and retention.The protocol includes patients from a single country, which might limit the generalisation to different healthcare systems.

## Introduction

### Background and rationale

 Breast reconstruction is an integral part of modern breast cancer treatment.^1 2^ Nevertheless, evidence for the effectiveness of breast reconstruction methods is lacking with respect to increasing quality of life and achieving high patient satisfaction, with a low complication rate and societal economic costs. The low evidence is reflected in the varying guidelines for breast reconstruction and unequal access to different methods that have been seen in a European study,^3^ as well as in a report published by the Swedish Breast Cancer Association.^4^ Techniques for breast reconstruction can roughly be divided into two categories: *autologous* and *implant-based* techniques. Three systematic reviews^5^,^7^ have concluded that patients seem to have a higher breast-related quality of life when reconstructed with autologous techniques compared with implant-based techniques. However, most of the included studies were retrospective, non-randomised, did not correct for other factors that might affect satisfaction, and had a short follow-up. Moreover, few high-quality studies compare long-term cost-effectiveness^8^ and the long-term need for revisions, corrections, and donor-site consequences. All of these factors are essential to create evidence-based guidelines, prioritise the usage of healthcare resources and to give the patients information on which they can base decisions of breast reconstruction. There are no ongoing trials registered in ClinicalTrials.gov comparing different categories of breast reconstruction technique head to head (https://clinicaltrials.gov/search?cond=breastreconstruction (search performed 22 July 2023)).

Randomised controlled trials (RCT) are generally thought to provide the most solid scientific evidence for treatment effects. However, there are barriers to conducting RCTs in breast reconstruction, making both recruitment and achieving unbiased and generalisable results a challenge.^9 10^ First, an RCT requires that there is solid uncertainty about which method achieves the best results. In the case of breast reconstruction, the operating surgeon must not prefer one method to another (*theoretical equipoise*)^11^ as this could result in both biased recruitment as well as biased outcomes if the included patients receive biased preoperative and postoperative information.^9^ The patient must also not have preformed ideas and clear preferences regarding the different methods (*principle of indifference*)^11^ based on, for example, other patients, patient organisations, and the media, as this also affects the recruitment and the results. Patients’ preferences can affect the external validity if a standard treatment, for example, implant-based breast reconstruction in non-irradiated patients,^12^ is compared with an alternative treatment, for example, autologous reconstruction, as only patients who prefer autologous reconstruction are likely to accept randomisation. Patients’ preferences could also reduce internal validity as randomisation to the (non-) preferred strategy could affect both adherence to the protocol (*reluctant acquiescence phenomenon*)^13^ and outcome. All these factors would lead to results that are not generalisable to the clinical population. This risk of bias and low internal and external validity illustrates why an RCT can be an inappropriate study design when comparing different categories of breast reconstruction.

A PubMed search on breast AND reconstruction, limited to RCTs, yields 419 results (10.07.2023).^14^ One-hundred and nine of them are RCTs concerning some aspect of breast reconstruction. The majority compared surgical variation within the same category of breast reconstruction technique, for example, one versus two stages or mesh versus no mesh in implant-based breast reconstruction and preoperative imaging versus no preoperative imaging in autologous breast reconstruction. Only four studies compare different categories of breast reconstruction techniques head to head^15^,^18^ and they all illustrate the aforementioned challenges with RCTs in breast reconstruction. For example, in the RCT performed in our department, the Gothenburg Breast Reconstitution trial (GoBreast),^18 19^ preintervention dropouts rates after randomisation varied between 12.5% and 23% in different groups, due to either the patient’s or surgeon’s preferences.

The study design partially randomised patient preference trial (RPPT) is an approach to diminish the impact of patients’ preferences, facilitate recruitment, increase patient centricity, decrease the risk of excluding large patient groups and make the results more generalisable to the clinical population, when preference-sensitive interventions are compared.^20^ In an RPPT, patients with a clear preference are treated accordingly and patients without a distinct preference are randomised in the traditional way. The RPPT design enables a more efficient inclusion of participants, and a clinically more representative study population, while maintaining a high external and internal validity.^20^ GoBreast II will mark the first use of an RPPT design to evaluate breast reconstruction methods.

### Choice of comparators

There is a myriad of different surgical options in breast reconstruction, such as different meshes and implants, as well as different pedicled or free flaps, but there are two main categories: implant based or autologous breast reconstruction. The two main categories are compared in this study.

### Research hypotheses

It is hypothesised that

patients are more satisfied with the reconstructed breast/s when an autologous deep inferior epigastric perforator (DIEP) flap is performed.although a ‘simpler procedure’, implant-based reconstruction entails a higher total number of operations and revisions long-term, compared with autologous DIEP-flap.although a procedure that is more costly for the healthcare system when it is performed, an autologous DIEP-flap is more cost-effective for society in the long-term perspective, due to the long-term effects and consequences of implants.

### Study objectives

The main overall purpose of breast reconstruction is to increase the woman’s quality of life, both physically and psychosocially. Therefore, the primary objective/outcome is to compare the two methods regarding patient-reported breast-specific quality of life and satisfaction. These measures are also part of the core outcome set for breast reconstruction developed by patients and professionals.^21^

The secondary objectives are to compare the two methods regarding complications, unplanned operations, corrections, cost-effectiveness and factors that might affect the primary outcome. Other secondary objectives are to improve the evidence for trial decision-making in breast reconstruction to improve the methodological design and process of future studies by means of a study within a trial (SWAT).^22^

### Trial design

GoBreast II is a partially RPPT with a superiority framework. Participants who accept randomisation will be allocated to one of the two methods. Participants who do not accept randomisation will be operated with their preferred method. Thus, the study has two cohorts: one randomised and one patient preference (figure 1). The trial is a single-centre study conducted at a university hospital in Sweden. It has embedded qualitative and health economic research questions.

**Figure 1 F1:**
[figure not shown]
The partially randomised patient preference trial design (RPPT) and allocation of the patients. Figure by [name], Department of Plastic and Reconstructive Surgery, Sahlgrenska University Hospital.

## Methods and analysis

### Reporting and preregistration

This protocol is reported in accordance with the Standard Protocol Items: Recommendations for Interventional Trials (SPIRIT) statement 2013^23^ (online supplemental appendix 1), including the SPIRIT-PRO extension^24^ (online supplemental appendix 2). The trial was registered at (ClinicalTrials.Gov identifier NCT06195865).

### Study setting

The study will be performed at Sahlgrenska University Hospital in Gothenburg, Sweden, where the Department of Plastic Surgery currently performs about 350 breast reconstructions yearly, both in the immediate and the delayed setting. In the catchment area of Sahlgrenska University Hospital, all patients diagnosed with breast cancer who have had or will receive a mastectomy and are considering a breast reconstruction are referred to this department. Among the referrals, potentially eligible participants will be invited to consider participation in the trial. According to the current Swedish guidelines,^12^ non-irradiated patients are offered mainly implant-based breast reconstruction and irradiated patients autologous techniques. The Swedish healthcare system is a publicly funded welfare-type healthcare system with a strong emphasis on equal access.

### Population

#### Recruitment and inclusion and exclusion criteria

Among the referrals to the department, potentially eligible participants will be invited to consider participation in the trial. Inclusion and exclusion criteria are given in figure 2.

**Figure 2 F2:**
[figure not shown]
Inclusion and exclusion criteria. ^1^Immediate breast reconstruction: to stop smoking when they are informed about the diagnosis and abstain from smoking at least 6 weeks postop. Delayed breast reconstruction: abstain from smoking 6 weeks preoperatively and 6 weeks postoperatively. ^2^Making a DIEP-flap impossible/an implant-based reconstruction unsuitable. ASA, American Society of Anesthesiologists classification; BMI, body mass index; DIEP, deep inferior epigastric perforator flap.

#### Sample size

The study is s a superiority trial based on the BREAST-Q domain *Satisfaction with the breast/s*.^25^,^27^ The clinically meaningful difference in BREAST-Q was set to 10 points. There are no anchor-based minimal important differences (MIDs) published for BREAST-Q, but the distribution-based MID is 4 for satisfaction with the breast/s.^28^ The SD was set to 18, as calculated according to US norms.^29^ If power is set to 0.80 and alpha to 0.05, the case-to-control ratio is 1, and a 20% dropout rate is expected, 62 patients are needed in each group (https://riskcalc.org/samplesize/). In the randomised cohort, 124 participants will be randomised 1:1. In the preference cohort, patients will be included until 62 participants have selected the least popular alternative (figure 3). This will result in an overall trial cohort with a minimum of 124 participants in each arm and enough participants in the subgroups *randomised* and *patient preference* to allow for analyses of differences.

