### Statistical methods

A detailed statistical analysis plan will be drafted early in the trial and finalised before primary outcome analysis. All analysis will be performed on an intention-to-treat basis and per-protocol analysis as sensitivity analysis. Descriptive data will be given as appropriate according to type of data and if it is skewed or not. This will also form the basis for statistical tests chosen to compare groups. Sensitivity analysis will be done were missing data in predictors will be handled by multiple imputation methods.^50^ Regression analysis preceded by collinearity check of potential predictors and performed to allow for correction for possible confounders. Residuals for each regression analysis will be checked for the assumptions of normal distribution and constant deviation along the predicted values. Subgroup analyses will be performed for the randomised and the preference cohort and for timing of reconstruction (immediate/delayed reconstruction) and for patients who unexpectedly will require radiotherapy. The statistical analysis will adhere to the Setting Intenartional Standards in Analysing Patient-Reported Outcomes and Quality of Life Endpoints in Cancer Clinical Trials (SISOQOL) framework.^51^ All tests will be two tailed and a p value of ≤0.05 will be considered to indicate a statistical significance.

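### The 62 per group does not follow from the stated inputs: 80% power after 20% dropout needs 64, and 62 gives about 78–79% in the randomised cohort

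*Protocol article*

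**What the plan says.** The Sample size section of the protocol article bases the calculation on the BREAST-Q domain for satisfaction with the breasts. Its inputs are:

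- Difference: "The clinically meaningful difference in BREAST-Q was set to 10 points".
- Standard deviation: "The SD was set to 18, as calculated according to US norms".
- Error rates: "If power is set to 0.80 and alpha to 0.05".
- Allocation: "the case-to-control ratio is 1".

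The conclusion is that "a 20% dropout rate is expected, 62 patients are needed in each group", with a link to an online calculator. The section then applies the figure: "In the randomised cohort, 124 participants will be randomised 1:1". It sets the same 62 as the target for the less chosen option in the preference cohort, which makes the overall minimum 124 per arm. The Statistical methods section settles the sidedness: "All tests will be two tailed and a p value of ≤0.05 will be considered to indicate a statistical significance".

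The article gives neither the number needed before dropout nor the way the 20% was applied.

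**The concern.** A sample size that allows for dropout should leave the required number of evaluable patients once the expected loss has occurred. Here it does not: 80% of 62 is 49.6, and the protocol's own inputs require 51. The 62 per group therefore falls slightly short of the power that the protocol attaches to it.

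The figure matters because it sets the size of the randomised cohort, the only comparison protected from confounding by patient preference, and because it recurs in the abstract and the preference-cohort target. A reader who repeats the calculation will get a different number.

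**Working it through.** **Inputs.** Difference 10, SD 18, power 0.80, alpha 0.05, ratio 1:1 and dropout 20% come from Sample size. Two-sided testing comes from Statistical methods.

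**Step 1: evaluable patients per group.** By the normal approximation,

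n = 2 × (1.960 + 0.8416)² × 18² / 10² = 50.86, so 51.

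The t distribution gives 51.84, so 52.

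**Step 2: reproducing the plan's 62.** Several routes were tried.

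| Route | Result per group |
|---|---|
| 51 × 1.2 | 61.2, so 62 |
| 51 / 0.8 | 63.75, so 64 |
| 52 × 1.2 (t) | 62.4, so 63 |
| 52 / 0.8 (t) | 65 |
| One-sided alpha, 40.06 before dropout | 48.1 (× 1.2) or 50.1 (/ 0.8) |

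Rounding up throughout, only the first route gives exactly 62. Multiplying by 1.2 adds 20% of the evaluable number. Retaining that number after 20% of those enrolled are lost requires division by 0.8. Division gives 64 or 65, so 62 is short by 2 per group (3 with t), or 4 in total (6 with t).

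**Step 3: power with 62 per group and 20% loss.** The number remaining is 62 × 0.8 = 49.6. The standard error of the difference is 18 × √(2/49.6) = 3.614. Then 10/3.614 = 2.767, and 2.767 − 1.960 = 0.807, which corresponds to a power of 79.0%. The t distribution gives 78.2%.

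In whole patients:

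| Remaining per group | Normal | t |
|---|---|---|
| 49 | 78.5% | 77.7% |
| 50 | 79.3% | 78.5% |
| 51 | 80.1% | 79.3% |
| 52 | 80.9% | 80.1% |
| 62 (no loss) | 87.1% | 86.6% |

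**Step 4: overall cohort.** With 124 per arm and 20% loss, 99.2 remain. The standard error is 18 × √(2/99.2) = 2.556. Then 10/2.556 = 3.913, and 3.913 − 1.960 = 1.953, a power of about 97%.

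**The case against.** The strongest reply is that the gap is too small to matter. By the normal approximation, which is the method that reproduces 62, the loss is 1.0 point of power. The SD is given as a whole number, and an SD of 17.7, which rounds to 18, would give 80.3% with 49.6 per group. The shortfall is therefore smaller than the rounding of an input. This stands as a statement about size, and it is why the point is minor. It does not make 62 the answer to the calculation as stated.

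Three stronger readings are tempting, and the document does not support them.

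- *The sponsor multiplied when it should have divided.* A reader might infer this from the exact match. The article shows no intermediate number, so the match is suggestive only. The point does not depend on it, because 49.6 is below 51 however 62 was reached.
- *The trial as a whole is underpowered.* The shortfall concerns the randomised cohort analysed alone. The protocol also plans an overall cohort of at least 124 per arm, for which it is immaterial on the same assumptions.
- *Power will be far lower because the department's earlier trial lost many patients before surgery.* Background and rationale reports that "preintervention dropouts rates after randomisation varied between 12.5% and 23% in different groups", and a reader might add those losses to the 20%. The Sample size section does not say that its 20% excludes such losses, so adding them may count them twice. The upper figure is the maximum over groups and should not be applied to both arms. The earlier trial was a conventional randomised trial of other comparisons, partly in irradiated patients, and its early losses came from patients' or surgeons' preferences. The present design directs patients with clear preferences to a separate cohort before randomisation.

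A request for separate assumptions on early and later loss would only ask for detail that an article may leave to the full protocol or analysis plan.

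**Conclusion.** The point holds as a minor arithmetic correction. On the stated inputs, two-sided testing and a 20% loss in each group, 64 per group are needed (65 with t), not 62. With 62, power in the randomised cohort analysed alone is about 79% (78% with t), which is 1 to 2 points below the stated 80%.

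The result rests on an unadjusted comparison of two means and on taking the SD as exactly 18. It says nothing about how the 62 was obtained, does not extend to the overall cohort, and gives no ground for predicting a larger loss of power.

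**What to change.** Restate the power in the Sample size section: after 20% dropout, 62 per group gives about 78–79% power in the randomised cohort. This changes one sentence and no recruitment target. Its only downside is a slightly less favourable stated power.

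If the sponsor prefers to keep 80%, the consistent figure is 64 per group, or 128 randomised (65 and 130 if the t distribution is used). That costs 4 more randomised patients (6 with t). The change should be carried through the abstract, the Sample size section and Figure 3, whose caption says that it gives the sample sizes. The sponsor should then also say whether the preference-cohort target moves with it. If it does, the overall minimum becomes 64 + 64 = 128 per arm; if it stays at 62, it becomes 64 + 62 = 126. In either case, showing the 51 (or 52) evaluable patients and the dropout step would let a reader repeat the calculation.

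### With 20% dropout, 62 women per group give about 78–79% power for a 10-point difference, slightly below the stated 80%

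*Protocol article*

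**What the plan says.** The Sample size section describes a "superiority trial based on the BREAST-Q domain" on satisfaction with the breast/s. Its inputs are:

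- Difference: "The clinically meaningful difference in BREAST-Q was set to 10 points".
- Variability: "The SD was set to 18, as calculated according to US norms".
- Error rates: "power is set to 0.80 and alpha to 0.05", with equal groups.
- Sidedness, from Statistical methods: "All tests will be two tailed".
- Loss and result: "a 20% dropout rate is expected, 62 patients are needed in each group", with a link to an online calculator.

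The article gives neither the number needed before dropout nor the formula used to allow for it.

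The figure of 62 is then used three times. Doubled, it is the randomised total (Abstract: "124 participants will be randomised"). It is the recruitment stop in the other cohort: "In the preference cohort, patients will be included until 62 participants have selected the least popular alternative". Added across the two cohorts, it gives the overall minimum of 124 per arm.

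**The concern.** If 20% of those enrolled are lost, 80% remain, so the number to enrol is the evaluable number divided by 0.8. Multiplying by 1.2 gives a smaller number that does not leave enough women after the loss. The stated 62 agrees with the second calculation and not with the first.

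At stake is whether the protocol's main planning sentence is true on its own terms. The sample size is fixed in this document and all its inputs are printed, so this is not a detail left to the analysis plan. The margin also has some practical relevance. The protocol's Background and rationale reports preintervention dropout of 12.5% to 23% in the department's first GoBreast trial, and Risks with the study names low retention as a concern. The loss that 62 per group can absorb at 80% power lies inside that range.

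**Working it through.** **Inputs.** Difference 10, SD 18, power 0.80, alpha 0.05, ratio 1 and dropout 20% (Sample size); two-sided tests (Statistical methods). No outside figure is used.

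**Step 1: evaluable women per group.**

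- Normal formula: n = 2 x (1.960 + 0.842)^2 x 18^2 / 10^2 = 50.86, so 51.
- t test (standardised difference 10/18): n = 51.84, so 52.

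**Step 2: reproduce the stated 62.**

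| Evaluable per group | x 1.2 | / 0.8 |
|---|---|---|
| 51 (normal) | 61.2, rounded up to **62** | 63.75, rounded up to 64 |
| 52 (t test) | 62.4, rounded up to 63 | 65 |

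One-sided alpha would need 41 evaluable, which inflates to 50 (x 1.2) or 52 (/ 0.8), so it does not explain 62. The match is 51 x 1.2 rounded up.

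**Step 3: what 62 delivers after 20% loss.** 62 x 0.8 = 49.6 evaluable per group.

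- Normal: standard error = 18 x sqrt(2/49.6) = 3.614. Then 10/3.614 = 2.767, and 2.767 - 1.960 = 0.807, giving power 0.790.
- t test: power 0.782.

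**Step 4: the loss at which 62 still gives 80% power.**

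- Normal: 1 - 50.86/62 = 18.0%. Keeping a whole 51 women allows 1 - 51/62 = 17.7%.
- t test: 1 - 51.84/62 = 16.4%. Keeping a whole 52 women allows 1 - 52/62 = 16.1%.

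**Step 5: figures consistent with 80% power at 20% loss.**

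- Normal: 64 per group, 2 x 64 = 128 randomised.
- t test: 65 per group, 2 x 65 = 130 randomised. Here 64 is not quite enough, because 64 x 0.8 = 51.2 is below 51.84.

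**The case against.** Four points can be made for the plan.

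1. **The inflation step is not printed.** A reader might infer that dropout was certainly applied by multiplying by 1.2. The document does not support that: it gives only the result and a calculator link. The numerical match makes this the likely route, and no more can be said. The shortfall does not depend on the route, because 62 x 0.8 is below 51 however 62 was reached.

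2. **The gap is smaller than the precision of the inputs.** By the normal formula, 49.6 per group gives 80% power at SD 18 x sqrt(49.6/50.86) = 17.78, which also rounds to 18. The protocol plans regression with correction for confounders. If baseline satisfaction were a covariate (an assumption, since it is not named), a correlation of sqrt(1 - 49.6/50.86) = 0.16 would recover the loss. This stands as a reason to call the error minor. It does not make the printed combination of 62, 20% and 80% correct, because the calculation as stated uses SD 18 and no covariate.

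3. **The preference-cohort 62 and the 124 per arm are minimums.** The more popular option will normally exceed 62, so the power given here is the floor for that cohort. This stands.

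4. **Pooling the cohorts leaves ample numbers.** 124 x 0.8 = 99.2 per arm, which gives about 97% power for 10 points. That is correct as arithmetic, but the pooled comparison is partly non-randomised, and 62 is presented as the number needed in each group. Pooling does not make that statement true.

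**Conclusion.** Wrong as written, but minor. Under the protocol's own inputs and two-sided testing, 62 per group with 20% dropout gives about 79% power (normal) or 78% (t test) for a 10-point difference, against the stated 80%. The shortfall is 2 women per group by the normal formula or 3 by t test.

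This applies to the comparison within the randomised cohort, and within the preference cohort if both options are at 62. It takes the 20% rate as given, assumes equal groups with equal loss, and makes no covariate adjustment.

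A reader might infer that the trial is materially underpowered, or that the overall comparison at 124 or more per arm falls short too. The documents support neither: the loss is 1 to 2 points of power, and the pooled numbers are well above what a 10-point difference needs.

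**What to change.** Preferred: keep 124 randomised and correct the statement. Say that 51 evaluable women per group are needed (52 by t test), and that 62 per group gives about 78–79% power for 10 points after 20% loss, or 80% power with up to about 16–18% loss. Name the test and the dropout formula used. This costs one or two sentences, a slightly less favourable power figure and no extra patients.

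Alternative: keep 80% power at 20% loss and change the numbers together, using one method throughout.

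- Normal formula: 64 per group, 128 randomised, preference-cohort minimum 64, overall minimum 64 + 64 = 128 per arm.
- t test: 65 per group, 130 randomised, preference-cohort minimum 65, overall minimum 65 + 65 = 130 per arm.

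This costs 4 or 6 more randomised women, at least the same number more in the preference cohort, and matching edits to the Abstract, the Sample size section and the sample-size figure.

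### The sample-size section says the two cohorts are large enough to analyse differences without saying which: method differences within a cohort fall just short of 0.80 power, and a cohort difference in method effect is not powered

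*Protocol article*

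**What the plan says.** The Sample size section describes a "superiority trial based on the BREAST-Q domain" for satisfaction with the breast/s. Its inputs are:

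- "The clinically meaningful difference in BREAST-Q was set to 10 points", with a note that "the distribution-based MID is 4 for satisfaction with the breast/s";
- "The SD was set to 18, as calculated according to US norms";
- "If power is set to 0.80 and alpha to 0.05", with equal groups and 20% dropout.

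The result is 62 per group. The randomised cohort therefore has 124 women allocated 1:1. The preference cohort recruits until 62 have chosen the less popular method, with no stated cap on the other arm. The section ends by saying that this gives at least 124 per arm overall and enough women in the two cohorts "to allow for analyses of differences".

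Statistical methods adds: "Subgroup analyses will be performed for the randomised and the preference cohort and for timing of reconstruction (immediate/delayed reconstruction"). It also says "All tests will be two tailed". It names no cohort-by-method interaction, and no power is given for any comparison between cohorts.

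**The concern.** The closing sentence of the Sample size section asserts that numbers are adequate for an analysis it does not define. Three meanings are possible: the method difference inside each cohort, a difference in overall level between cohorts, or a difference between cohorts in the method effect. The third is the one specific to a partially randomised preference design. The Introduction argues that preference can affect adherence and outcome, so a natural question is whether implant versus autologous reconstruction has the same effect in women who accept randomisation and in women who choose.

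That question is a difference of two differences. With equal cell sizes its variance is twice that of the comparison the trial was sized for. A reader told that numbers are sufficient could take a non-significant cohort difference as informative when the data could not exclude one as large as the trial's own target. Separately, the 62 per arm does not quite deliver the stated 0.80 even within one cohort once the planned dropout is taken off.

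**Working it through.** **Inputs** (Sample size, Statistical methods): difference 10 points, SD 18, power 0.80, two-sided alpha 0.05, 1:1 allocation, 20% dropout, 62 per arm in the randomised cohort and at least 62 per arm in the preference cohort.

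**1. Reproducing the stated 62.** Evaluable n per arm = 2 x 18² x (1.960 + 0.842)² / 10² = 50.86, rounded up to 51.
- 51 x 1.2 = 61.2, rounded up to 62, the stated figure.
- 51 / 0.8 = 63.75, rounded up to 64, the number that leaves 51 after losing 20%.

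The plan's figure is reproduced by multiplying by 1.2. It is two per arm short of what 20% dropout requires.

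**2. Method difference within one cohort.** 62 x 0.8 = 49.6 evaluable per arm.
- SE = 18 x sqrt(2/49.6) = 3.61, and 10/3.61 = 2.77.
- Power = Phi(2.77 - 1.96) = 0.79. The noncentral t gives 0.78.

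**3. Overall mean difference between cohorts.** 99.2 evaluable per cohort.
- SE = 18 x sqrt(2/99.2) = 2.56, and 10/2.56 = 3.91.
- Power for 10 points is about 0.97.

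**4. Cohort difference in method effect.** SE = 18 x sqrt(sum of 1/n over the four cohort-by-method cells). At minimum recruitment with 20% dropout:
- SE = 18 x sqrt(4/49.6) = 5.11.
- For 10 points: 10/5.11 = 1.956, power 0.50 (noncentral t 0.495).
- For 5 points, power is 0.16. For 4 points, power is 0.12.
- Detectable with 80% power: 2.80 x 5.11 = 14.3 points.
- Half-width of the 95% CI: 1.96 x 5.11 = 10.0 points.

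**5. Sensitivity of step 4** at 10 points, unadjusted:

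| Scenario | SE | Power |
|---|---|---|
| 49.6 in every cell | 5.11 | 0.50 |
| Popular preference arm doubled (99.2) | 4.78 | 0.55 |
| Popular preference arm tripled (148.8) | 4.67 | 0.57 |
| Popular preference arm unlimited | 4.43 | 0.62 |
| No dropout, 62 in every cell | 4.57 | 0.59 |
| No dropout, popular preference arm unlimited | 3.96 | 0.71 |

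Baseline adjustment with an assumed correlation of 0.3 to 0.5 (not in the protocol) would raise the first row to about 0.54 to 0.62.

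**6. Size needed.** 80% power for a 10-point interaction needs 4 x 18² x (2.80)² / 10², about 102 evaluable per cell. At 20% dropout that is about 128 enrolled per cell (102/0.8 = 127.5), against 62 planned.

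**The case against.** The strongest reply is that the sentence never mentions an interaction. Each cohort is given the per-arm number calculated just above it, so the most direct reading is that each cohort can support its own method comparison. The subgroup sentence in Statistical methods fits that reading. On it, power is 0.78 to 0.79 and the sentence is close to true. It is also true for an overall level difference between cohorts (about 0.97), and the Study within a trial section plans contrasts between cohorts, on baseline characteristics. All of this stands. It would be wrong to say that no reading supports the sentence.

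Two further points also stand. The 10 points is the target for the method difference, and applying it to an interaction is an assumption made here. It is generous, since smaller interactions have much less power. And choices of model and labels of exploratory status can properly be left to the analysis plan, so their absence from this article is not the criticism.

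A reader might also infer that the trial intends to use a null cohort difference to justify combining the cohorts. The protocol does not say so: the overall cohort is described unconditionally, and nothing makes it depend on an interaction test. Nor does the protocol claim adequate numbers for the immediate/delayed subgroup. It only lists that analysis, so low power there contradicts nothing.

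The objection does not remove the unqualified adequacy statement. It appears in the sample-size section, leaves its object undefined, and is untrue for the comparison most specific to this design.

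**Conclusion.** The concern holds as a matter of an undefined and partly unsupported adequacy statement, not as a failure of the main design. Within a cohort, 62 per arm gives about 0.78 to 0.79 power for 10 points after 20% loss, a small shortfall from 0.80 that comes from how dropout was applied. For a cohort difference in method effect, power at 10 points is about 0.50 at minimum recruitment with 20% dropout. It rises to at most about 0.71 under the most favourable recruitment and retention possible under the stated rule. The detectable difference is about 14 points, larger than the 10 points the trial calls clinically meaningful.

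These figures assume a common SD of 18, two-sided 5% tests, no covariate adjustment and, for the interaction, a 10-point effect. The amendment is worth making because the sentence gives assurance on a central question of a preference trial that the numbers do not provide.

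**What to change.** In the Sample size section:

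1. Say which differences the closing sentence refers to.
2. Restate power for a 10-point method difference within one cohort as about 78-79% after 20% dropout.
3. State that a difference between cohorts in the method effect is not powered: about 50% at 10 points under minimum recruitment and 20% dropout, with an expected 95% CI of about +/-10 points.

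In Statistical methods or the analysis plan, estimate that difference as a cohort-by-method interaction with a 95% CI, label it exploratory, and state that non-significance will not be read as absence of a preference effect.

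The cost is wording only. Recruitment targets and data collection do not change, but the stated power becomes less favourable.
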